## Abstract

**Background:**

Persons with spinal cord injury (SCI) are at heightened risks of developing unfavorable cardiometabolic consequences due to physical inactivity. Functional electrical stimulation (FES) and surface neuromuscular electrical stimulation (NMES)-resistance training (RT) have emerged as effective rehabilitation methods that can exercise muscles below the level of injury and attenuate cardio-metabolic risk factors. Our aims are to determine the impact of 12 weeks of NMES + 12 weeks of FES-lower extremity cycling (LEC) compared to 12 weeks of passive movement + 12 weeks of FES-LEC on: (1) oxygen uptake (VO_2_), insulin sensitivity, and glucose disposal in adults with SCI; (2) skeletal muscle size, intramuscular fat (IMF), and visceral adipose tissue (VAT); and (3) protein expression of energy metabolism, protein molecules involved in insulin signaling, muscle hypertrophy, and oxygen uptake and electron transport chain (ETC) activities.

**Methods/Design:**

Forty-eight persons aged 18–65 years with chronic (> 1 year) SCI/D (AIS A-C) at the C5-L2 levels, equally sub-grouped by cervical or sub-cervical injury levels and time since injury, will be randomized into either the NMES + FES group or Passive + FES (control group). The NMES + FES group will undergo 12 weeks of evoked RT using twice-weekly NMES and ankle weights followed by twice-weekly progressive FES-LEC for an additional 12 weeks. The control group will undergo 12 weeks of passive movement followed by 12 weeks of progressive FES-LEC. Measurements will be performed at baseline (B; week 0), post-intervention 1 (P1; week 13), and post-intervention 2 (P2; week 25), and will include: VO_2_ measurements, insulin sensitivity, and glucose effectiveness using intravenous glucose tolerance test; magnetic resonance imaging to measure muscle, IMF, and VAT areas; muscle biopsy to measure protein expression and intracellular signaling; and mitochondrial ETC function.

**Discussion:**

Training through NMES + RT may evoke muscle hypertrophy and positively impact oxygen uptake, insulin sensitivity, and glucose effectiveness. This may result in beneficial outcomes on metabolic activity, body composition profile, mitochondrial ETC, and intracellular signaling related to insulin action and muscle hypertrophy. In the future, NMES-RT may be added to FES-LEC to improve the workloads achieved in the rehabilitation of persons with SCI and further decrease muscle wasting and cardio-metabolic risks.

**Trial registration:**

ClinicalTrials.gov, NCT02660073. Registered on 21 Jan 2016.

## Background

Spinal cord injury (SCI) is a devastating medical condition that results in reduced aerobic fitness, glucose intolerance, and insulin resistance due to autonomic dysfunction, muscle wasting, increased regional and total body fat mass, and relative inactivity [1]. Of the more than 46,000 veterans with SCI-related disability, > 60% are overweight or obese, > 50% are glucose intolerant, and 20% are diabetic [2, 3]. There are 11,000–12,000 new cases of SCI in the United States annually. The prevalence of individuals with SCI has been estimated to be 250,000–400,000 with an estimated 14% growth in prevalence since 1988 [4, 5]. In the last two decades, costs of SCI in the United States have increased with a concomitant decline in mortality over the first year after SCI [1]. The average initial charge per case is in the range of $342,000–$1,048,000 for acute stabilization and rehabilitation, with annual charges thereafter in the range of $41,000–$182,000 [4, 6, 7]. It has been estimated that the estimated lifetime costs that result from SCI is 7.3–12 million dollars [4, 6].

The Centers for Disease Control and Prevention (CDC) and the American College of Sports Medicine have recommended 30 min of daily exercise to prevent the occurrence of health-related and obesity-related secondary complications [8]. Furthermore, guidelines were recently published by the International Spinal Cord Injury Society (ISCoS) suggesting 2–3 days per week of moderate to vigorous physical activity to lessen secondary co-morbidities [9]. However, there are several barriers that interfere with maximizing the benefits of any exercise protocol [10]. To offset some of these barriers, exercising skeletal muscle below the level of injury may enhance several cellular activities and whole-body metabolism [11–13]. Skeletal muscles serve as a large endocrine gland that controls interplay between musculoskeletal systems and other physiological systems [14–16]. Previous work demonstrated that skeletal muscle hypertrophy releases important myokines that may regulate atrophic pathways, bone, and endocrine glands. Thus, it is crucial to maintain the skeletal muscle vitality sublesionally to maintain the integrity of other physiological systems [11–13].

Functional electrical stimulation (FES) is a form of neuromuscular electrical stimulation (NMES) which provides stimulation of selected muscles in a coordinated manner resulting in a functional pattern such as walking, cycling, or rowing. This is contrary to surface NMES which is used for a single or multiple muscle groups to exercise or to move specific joint, but without the intention of producing a functional or coordinated movement [17]. FES-lower extremity cycling (LEC) is limited by the low exercise intensity, low peak oxygen uptake (0.4 L/min), and rapid muscle fatigue, which renders FES-LEC training a suboptimal modality to increase gain in lean mass and improve metabolic health after SCI [18, 19]. This may result from a mismatch when converting metabolic energy into mechanical energy.

Neuromuscular electrical stimulation (NMES) has been used to evoke exercise-induced resistance training (RT) using regular ankle weights in individuals with chronic SCI [20–24]. Several research groups demonstrated the efficacy of this approach in evoking robust muscle hypertrophy [21, 24, 25]. Dudley et al. showed that eight weeks of twice-weekly NMES RT reverted knee extensor muscle size to 75% of original size at six weeks after SCI [21]. Follow-up studies reported a 35–39% increase in muscle hypertrophy and 33% fatigue resistance of the trained knee extensors [22, 23]. Gorgey et al. noted that 12 weeks of twice-weekly NMES RT elicited an increase in skeletal muscle size of > 35%, decreased IMF and VAT by 25%, and increased insulin sensitivity and insulin growth factor-1 (IGF-1) by 25% [23]. Finally, Ryan et al. noted improvement in mitochondrial capacity by 25% following 16 weeks of twice-weekly evoked NMES RT in persons with chronic complete SCI [24]. A recent study demonstrated that 16 weeks of NMES-RT combined with testosterone replacement therapy (TRT) resulted in a 43% muscle hypertrophy of the knee extensor and 21% increase in thigh muscle cross-sectional area (CSA) accompanied with 14–17% increase in daily basal metabolic rate (BMR) compared to TRT only. [25]

The objectives of the current trial are to determine the impact of evoking skeletal muscle hypertrophy using surface NMES and ankle weights before conducting FES-LEC on oxygen uptake, insulin sensitivity, and glucose effectiveness (primary endpoint variables) compared to those who undergo passive movement and FES training only. The primary question is: does evoking skeletal muscle hypertrophy lead to improvement in metabolic health benefits as outlined in Fig. 1? This prospective randomized clinical trial will also shed light on the mechanism and signaling pathways responsible for evoking hypertrophy, enhancing energy, and substrate utilization as well as improving glucose metabolism.

**Fig. 1 Fig1:**
[figure not shown]
Rationale of the study. Briefly summarizes the negative impacts of SCI on body composition and cardiometabolic prolife and how adding NMES-RT to FES-LEC training may help to alleviate these health-related consequences and serve as a rehabilitation approach for persons with SCI

We hypothesize that the addition of 12 weeks of NMES combined with RT before FES-LEC will evoke skeletal muscle hypertrophy, decrease IMF and visceral fat, and enhance gains in aerobic fitness and insulin sensitivity observed during a subsequent 12-week period of exercise by FES-LEC. We also hypothesize that when NMES RT is administered before FES-LEC, the intracellular signaling related to insulin action (IRS1, Glut4) and muscle growth (Akt and mTOR) will be improved. These effects of NMES RT may further enhance the beneficial actions of FES-LEC on metabolic profile, body composition profile, and mitochondrial electron transport chain (ETC) and intracellular signaling related to insulin action and muscle growth.

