**Fig. 2 Fig2:**
[figure not shown]
The study timeline and procedure are highlighted. After screening and consent, participants will be randomized into one of two testing groups. Each participant will undergo baseline testing (B) before beginning NMES + FES or Control + FES. Each group will then be tested for metabolic, body, and muscle composition (P1) after a 12-week period. Each group will then complete 12 weeks of FES followed by another bout of testing (P2)

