### Passive range of motion for control

A member of the research team supports the leg proximal to the ankle joints and moves it from 90° knee flexion close to full knee extension. The leg will be maintained up for 5 s and returned down for 5 s. The passive movements will be repeated in the same fashion described in RT protocol: 10 reps for the right leg followed by 10 reps for the left leg for a total of four sets of 10 reps.

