### Statistical analyses

T-tests and Pearson chi-square tests will be used to compare characteristics that may act as confounding variables, including age, level of injury, time since injury, %FM, as well as the three outcome variables (Si, Sg, VO_2_) to ensure that each group is not different with respect to each variable at baseline. A repeated-measures ANOVA will be performed with glucose effectiveness as the primary study outcome and effects for treatment group (NMES + FES versus control), time (baseline and post-interventions 1 and 2), and the interaction between the two factors included in the model. Similar repeated measured ANOVA models will be fit with each of the body composition, metabolic profile, protein expression, and ETC measures (Aim 3). All statistical analysis will be performed at the 0.05 level with SAS V9.4 (Cary, NC, USA).

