In conclusion, the current clinical trial endeavors to increase the cardio-metabolic benefits of FES-LEC through the addition of NMES-RT. This may result in improvement of aerobic fitness and metabolic health and reduce the severity of chronic secondary health-related consequences. The study will provide mechanistic insights regarding molecular underpinnings of the benefits of the two different paradigms of electrical stimulation to chronically paralyzed muscles. One paradigm is mimicking RT using a weight-lifting approach and the other generates low tension stimulation mimicking aerobic-type training. It will be of interest to our population to understand the additive effects of both approaches on the cardio-metabolic outcome variables in persons with SCI. This could be simply integrated as an effective rehabilitation intervention in the clinical setting shortly after completion of the study.

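### The hypothesis that NMES-RT enhances gains during FES-LEC has no matching test: the planned group-by-time interaction can be significant from a phase-1 NMES effect alone

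*Protocol article*

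**What the plan says.** **Hypothesis.** In the Background, after Fig. 1, adding 12 weeks of NMES-RT before FES-LEC is expected to "enhance gains in aerobic fitness and insulin sensitivity observed during a subsequent 12-week period of exercise by FES-LEC".

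**Arms.** Under Methods/Design in the Abstract, the NMES + FES arm receives "12 weeks of evoked RT using twice-weekly NMES and ankle weights followed by twice-weekly progressive FES-LEC for an additional 12 weeks". For the comparator, "The control group will undergo 12 weeks of passive movement followed by 12 weeks of progressive FES-LEC". The movement is passive throughout: "A member of the research team supports the leg proximal to the ankle joints and moves it" (Passive range of motion for control).

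**Visits.** Both arms are measured between the two phases: "Each group will then be tested for metabolic, body, and muscle composition (P1) after a 12-week period" (Fig. 2 legend).

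**Analysis.** The repeated-measures ANOVA has effects for treatment group, "time (baseline and post-interventions 1 and 2), and the interaction between the two factors included in the model" (Statistical analyses). Glucose effectiveness is the primary outcome, and similar models are planned for the other measures. No contrast between visits is tied to any hypothesis.

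**Wider objective.** The Background also sets a broader aim: NMES-RT before FES-LEC, "compared to those who undergo passive movement and FES training only".

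**The concern.** The hypothesis is about what happens while both arms are cycling. It predicts a larger P1-to-P2 gain after NMES-RT than after passive movement. The interaction over three visits asks something else, namely whether the two arms' profiles over B, P1 and P2 are parallel. If NMES-RT does anything in the first 12 weeks, they are not parallel, whatever happens later.

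Write a for the phase-1 NMES effect and b for the FES-LEC gain. If a persists and b is the same in both arms, the arms stand at a + b and b at P2. They differ by a, and cycling was not enhanced.

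The two readings lead to different advice. One is that NMES-RT should come first because it makes cycling work better. The other is that a block of NMES-RT has a benefit of its own that lasts. The test as fixed cannot tell them apart.

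**Working it through.** **Inputs** (Sample size section)
- Glucose effectiveness: pilot means 0.01716 and 0.02258, variance 0.0001 (SD 0.01), f = 0.271, correlation r = 0.3735.
- Insulin sensitivity f = 0.313 and VO2 f = 0.432, r = 0.4 for both.
- 38 completers, taken as n = 19 per arm; alpha 0.05.

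**The plan's own figure**
- f = (0.02258 − 0.01716)/(2 × 0.01) = 0.271, so the pilot change is 0.542 SD = 2f.
- With N = 38 and m = 3 visits, λ = f²Nm/(1 − r) = 0.271² × 38 × 3/0.6265 = 13.36. On 2 and 72 df the power is 90.4%, so 38 reproduces. 38/0.8 = 47.5, rounded up to 48, also reproduces.

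**Phase-1 effects used** (a = 2f, in SD)
- Glucose effectiveness 0.542; insulin sensitivity 2 × 0.313 = 0.626; VO2 2 × 0.432 = 0.864.
- The conversion can be checked only for glucose effectiveness. For the other two it is an assumption, because no means or variances are given.

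**Zero enhancement, gain fully retained.** Arm differences at B, P1 and P2 are D = (0, a, a). Assume compound symmetry and no change in controls during passive movement.
- Interaction: λ = (n/2) Σ(D − D̄)²/(1 − r). Here Σ(D − D̄)² = 2a²/3, so λ = na²/[3(1 − r)]. The critical F on 2 and 72 df is 3.12.
- Contrast between two visits: SE = √[2(1 − r)] × √(2/n) = 0.363 SD at r = 0.3735 and 0.355 SD at r = 0.4, on 36 df.

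| Outcome | a (SD) | r | λ | Interaction significant | B-to-P2 contrast significant | P1-to-P2 contrast significant |
|---|---|---|---|---|---|---|
| Glucose effectiveness | 0.542 | 0.3735 | 19 × 0.542²/(3 × 0.6265) = 2.97 | 31% | 31% | 5% |
| Insulin sensitivity | 0.626 | 0.4 | 19 × 0.626²/(3 × 0.6) = 4.14 | 41% | 40% | 5% |
| VO2 | 0.864 | 0.4 | 19 × 0.864²/(3 × 0.6) = 7.88 | 69% | 66% | 5% |

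A simulation of 20,000 trials for glucose effectiveness gave 31%, 31% and 4.8%.

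**Other retention patterns**
- Gain fully lost by P2, D = (0, a, 0): Σ(D − D̄)² is again 2a²/3, so the interaction rates are the same 31%, 41% and 69%. The true P1-to-P2 difference is now −a, the opposite of enhancement.
- Half lost, D = (0, a, a/2): 24%, 32% and 56%. The true P1-to-P2 difference is −a/2.

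**Why 31% and not the planned 90%.** Here a is an arm difference present at two of three visits, which gives λ = 2.97 and not 13.36. For the retained pattern to reach λ = 13.36, a² = 13.36 × 3 × 0.6265/19 = 1.32, so a = 1.15 SD. At that size the interaction would be significant in about 90% of trials, still with zero enhancement.

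**Precision of the matching contrast**
- The 95% interval for the P1-to-P2 difference has half-width 2.03 × 0.363 = 0.74 SD.
- 80% power needs a noncentrality of about 2.88, so the detectable difference is 2.88 × 0.363 = 1.05 SD (r = 0.3735).

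**The case against.** **The arms are meant to differ by a training block.** A reader might infer that 24 versus 12 weeks of active training is an accidental confounder. The documents do not support that. The Abstract aims and the Background objective set out an add-on comparison, NMES-RT plus FES-LEC against passive movement plus FES-LEC. The overall comparison answers that objective. It does not answer the narrower hypothesis about gains made during cycling.

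**Follow-up contrasts are usually left to the SAP.** The P1-to-P2 difference is part of the two-degree-of-freedom interaction, P1 is measured in both arms, and an SAP that is not shown may name the contrast. This stands as far as it goes: the trial remains interpretable. But the article fixes both a hypothesis and a test, and the two do not match. That is more than missing detail.

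**The percentages are not error rates of the planned test.** This is correct. In every scenario above NMES-RT truly has an effect, so rejecting parallel profiles is right. A reader might take 31% to 69% as an inflated type-1 error or a fixed rate of false enhancement claims. Neither follows, since the article nowhere says that a significant interaction will be reported as enhancement.

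**Retention is uncertain.** The Limitations section itself raises the loss of benefit once training stops. That makes full retention an assumption. It does not rescue the test, because full loss gives the same interaction rates.

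**The conclusion does not claim enhancement.** It speaks of the wish to "understand the additive effects of both approaches on the cardio-metabolic outcome variables in persons with SCI". Additive effects are the a + b versus b case, with no enhancement, so that sentence is compatible with retained benefit and needs no change.

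**Conclusion.** The point holds as a mismatch between one stated hypothesis and the stated test. The hypothesis predicts a larger P1-to-P2 gain in the NMES arm. A significant interaction over B, P1 and P2 cannot support that, because it arises at the same rate whether the phase-1 gain is kept with equal FES-phase gains or lost entirely by P2.

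The rates of about 31%, 41% and 69% rest on compound symmetry, d = 2f, no change in controls during passive movement and 19 completers per arm. The 5% for the P1-to-P2 contrast applies to the full-retention case. Insulin sensitivity and VO2 (as aerobic fitness) are the outcomes that the hypothesis names; glucose effectiveness is shown because it is the primary outcome of the ANOVA.

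The design is not at fault, and data collection need not change. The change is worth making because it costs little and prevents an unsupported conclusion.

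**What to change.** In Statistical analyses, tie each claim to its own contrast:
1. **Enhancement of FES-LEC gains:** the between-arm difference in P1-to-P2 change, reported with its confidence interval.
2. **Effect of NMES-RT alone:** the arm difference at P1, before either arm has cycled in training.
3. **Total effect of adding the 12-week NMES-RT block:** the arm difference at P2, described as 24 versus 12 weeks of active training and not as evidence of enhanced cycling gains.

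The closing paragraph of the Limitations section can stay as it is.

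The cost is wording and one named contrast from visits already scheduled. The downside is that enhancement becomes harder to show: with 19 per arm only about 1.05 SD is detectable at 80% power. The plan should say so, and should not treat a non-significant contrast as showing equal gains.

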048	TBR			

*C* completed, *NA* not assigned for #008, 025, and 031, *TBR* to be recruited later

Before baseline 1, randomization was performed into NMES + FES or PM + FES groups. Post-intervention 1 (*n* = 23) was conducted after 12 weeks of intervention of either NMES or PM. Post-intervention 2 (*n* = 20) was conducted after 12 weeks of FES

Additionally, MRI scans will be obtained for trunk VAT, lower extremity skeletal muscles, and IMF CSAs [2, 3]. Participants will then be escorted to the VCU CRC and will remain in the CRC overnight for metabolic testing. This procedure will be used for the three study visits (baseline and post-interventions 1 and 2). Resting blood pressure and fasting metabolic labs will be obtained including HbA1c, as well as lipid panels, C-reactive protein (CRP), interleukin-6 (IL-6), tumor necrosis factor alpha (TNF-α), and free fatty acids (FFA). This will be followed by an intravenous glucose tolerance test (IVGTT). The vastus lateralis muscle will be biopsied to measure proteins expression and myosin heavy chain expression and to determine mitochondrial ETC and enzymatic activities. The design of the study is outlined in Fig. 2.

**Fig. 2 Fig2:**
[figure not shown]
The study timeline and procedure are highlighted. After screening and consent, participants will be randomized into one of two testing groups. Each participant will undergo baseline testing (B) before beginning NMES + FES or Control + FES. Each group will then be tested for metabolic, body, and muscle composition (P1) after a 12-week period. Each group will then complete 12 weeks of FES followed by another bout of testing (P2)

### Recruitment strategy

The recruitment process started in October 2015 and will end in September 2020. Forty-eight participants will be randomly assigned into either NMES + FES or Control + FES groups for 24 weeks. The participants will be matched based on level of injury (tetraplegia versus paraplegia) and time since injury (less than versus more than 10 years) using block randomization using a 2 × 2 design developed by the study statistician. Randomization was conducted using n-query computer program at the baseline before enrollment in the trial (Table 1). Current recruitment status is outlined in Table 2.

**Table 2 Tab2:** The breakdown of the number of persons who have been contacted for the study, who have completed the study, or are currently actively participating in the study. All others have either failed screening or withdrawn from the study

	Study period					
	Pre-Enrolment		Enrolment	Baseline	Post-intervention	
Timepoint**	1	2			1	2
Pre-enrolment:	**536**					
Not-interested	**354**					
Expressed interest	**182**					
Phone screen Failure		**68**				
Physical screen failure		**50**				
Qualified and Enrolled		**64**				
Enrolment [1 = a +b]			**64**			
No Show ^(a)^			29			
Consented ^(b)^ [2=c +d + e + F]			**35**			
Screen Failure ^(c)^			5			
Withdrawn ^(d)^			6	3	1	2
*Completed* ^*(e)*^			21			
*Currently Active* ^*(f)*^			3			
Pending future enrollment ^(g)^			13			
Total sample size [3=b +g]			**48**			
Interventions:						
[NMES+FES]			15	14	13	12
[Control + FES]			15	13	13	12
Assessments:						
[Body Composition Variables]				X	X	X
[Metabolic variables]				X	X	X
[Muscle Biopsy variables]				X	X	X
[Torque and fatigue variables]				X	X	X

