### Sample size

We have acquired pilot data for all outcomes of this project. Glucose effectiveness possesses the smallest effect size from baseline to follow-up with NMES-RT showing a mean baseline effectiveness of 0.01716 and post-treatment mean of 0.02258. Cohen’s *f* was found to be 0.271 using a sample variance of 0.0001 [25]. Assuming the correlation between the pre- and post-treatment measurements is 0.3735 and three total measurements are acquired, 38 individuals will need to complete the study at 90% power using a Type-1 error rate of 0.05. At least 48 participants will need to be recruited, adjusting for a 20% dropout rate. All sample sizes were calculated using the software G*Power (V3.1.9.2). A sample size of 24 was calculated using insulin sensitivity data without regard to dropout rate.

Other factors, such as insulin sensitivity and VO_2_, are considered; each representing larger effect sizes than glucose effectiveness (*f* = 0.313 and *f* = 0.432, respectively). Our study would result in a power of 97.51% and 99.82% for observing the baseline to follow-up difference between the NMES + FES and Control + FES groups, provided the correlation between baseline and follow-up measurements are 0.4 for the outcomes.

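### Table 2 reaches its total sample size of 48 by counting five screen failures, whereas the text and the power calculation need 48 randomised

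*Protocol article*

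**What the plan says.** The Recruitment strategy section of the protocol article states: "Forty-eight participants will be randomly assigned into either NMES + FES or Control + FES groups for 24 weeks". The Abstract also says that 48 persons will be randomised.

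The Sample size section sets the requirement: "38 individuals will need to complete the study at 90% power using a Type-1 error rate of 0.05". It then inflates for loss: "At least 48 participants will need to be recruited, adjusting for a 20% dropout rate". It makes no separate allowance for people who consent and then fail screening.

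Table 2, in the Recruitment strategy section, gives the status to date and projects the final size. Its key defines consented (b) as the sum of screen failures (c), withdrawn (d), completed (e) and currently active (f): 5 + 6 + 21 + 3 = 35. Pending future enrolment (g) is 13. The closing line, "Total sample size [3=b +g"], gives 48. The arm rows show 15 + 15 at enrolment, 14 + 13 at baseline, 13 + 13 at post-intervention 1 and 12 + 12 at post-intervention 2.

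The Table 1 footnote lists some study numbers as "not assigned for #008, 025, and 031", in numbering whose last visible row is 048. It also reports 23 participants at post-intervention 1, and "Post-intervention 2 (*n* = 20) was conducted after 12 weeks of FES".

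**The concern.** The number 48 is used in two senses. In the text and in the dropout inflation it means people who enter the randomised comparison. In Table 2 it means people who have consented, including those who then failed screening, plus those still to come. A person who fails screening before assignment cannot become a completer and is not a dropout in the sense of the 20% allowance.

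If the team works to Table 2's projection of 13 more people, the trial ends up smaller than the text promises and falls below its own completer requirement. The article describes recruitment as still open, so which number guides the remaining enrolment matters in practice.

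**Working it through.** **1. Reproducing the plan's 38 and 48.** Inputs from the Sample size section: means 0.01716 and 0.02258, variance 0.0001 (SD 0.01), correlation 0.3735, three measurements, alpha 0.05, and "Cohen’s *f* was found to be 0.271 using a sample variance of 0.0001". There are two groups.

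- Effect size: f = (0.02258 − 0.01716) / 0.01 / 2 = 0.271, as stated.
- Repeated-measures group-by-time interaction, with k = 2 groups, m = 3 measurements and sphericity assumed: λ = f²·N·m/(1 − ρ), df1 = (k − 1)(m − 1) = 2, df2 = (N − k)(m − 1).
- At N = 38: λ = 0.0734 × 38 × 3 / 0.6265 = 13.4, df2 = 72, power 0.904. This is the smallest N that reaches 0.90, so the 38 reproduces.
- Dropout: 38 / 0.8 = 47.5, rounded up to 48. This reproduces too, and it leaves no room for any other kind of loss.

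**2. Checking Table 2's sums.**

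- Consented: 5 + 6 + 21 + 3 = 35. Total: 35 + 13 = 48. Both add up.
- Assigned: 15 + 15 = 30 = 35 − 5. The five screen failures are in neither arm.
- Withdrawals by time point are 3, 1 and 2: 30 − 3 = 27 (14 + 13), 27 − 1 = 26 (13 + 13), 26 − 2 = 24 (12 + 12). All six withdrawals therefore come after assignment, and the 24 equals 21 completed + 3 active.

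**3. What Table 2's total implies if enrolment stops there.**

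| Quantity | Arithmetic | Result |
|---|---|---|
| Most randomised | 30 + 13 | 43 |
| Most completers | 21 + 3 + 13 | 37 |
| Completers with 20% loss among the 13 | 24 + 13 × 0.8 = 34.4 | about 34 |

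Power by the formula in step 1:

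| Completers | λ | df2 | Power |
|---|---|---|---|
| 38 | 13.4 | 72 | 90.4% |
| 37 | 13.0 | 70 | 89.5% |
| 34 | 12.0 | 64 | 86.6% |

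**4. What the text's 48 implies.** Still to randomise: 48 − 30 = 18, not 13. Completers: 24 + 18 = 42 with no further loss, or 24 + 18 × 0.8 = 38.4, about 38, with 20% loss. This agrees with the Sample size section.

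**5. Cross-check with the Table 1 footnote.** It lists three unassigned numbers; Table 2 has five screen failures. It gives 20 at post-intervention 2; Table 2 has 21 completed. Its 23 at post-intervention 1 fits Table 2 if the 3 active participants had not yet reached that visit (26 − 3 = 23).

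**The case against.** Table 2 is introduced as the current recruitment status, so it can be read as a snapshot that does not govern the design. The Abstract and the Recruitment strategy text both commit to randomising 48, and the Sample size section makes 48 a minimum. On that view Table 2 carries a mislabelled line and nothing more. Part of this stands: nothing in the article says that enrolment will close at Table 2's total. But the table does more than report status. It projects a final size and a number still to come, and both conflict with the paragraph above it.

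A reader might infer three stronger things that the documents do not support:

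- **That 38 completers cannot be reached.** This holds only if enrolment stops at Table 2's total. If 18 more are randomised, the plan is restored.
- **That the 20% allowance is already spent.** Six of 30 assigned is 20%, which is dropout running at the planned rate. In people, the allowance is 48 − 38 = 10, of which 6 are used and 4 remain. On Table 2's count, the 5 screen failures exceed those 4 by one, which is the best-case shortfall.
- **That the Table 1 footnote confirms the ceiling of 43.** It lists three unassigned numbers. If numbering ends at 048, up to 45 could be assigned, and 45 − 6 = 39 is above 38. The body of Table 1 is not available here, so three against five cannot be settled. The ceiling of 43 rests on Table 2 alone.

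**Conclusion.** Table 2's total is wrong as written: it conflicts with the stated number to be randomised and with the derivation of 48. Taken at its word, it gives at most 43 randomised instead of 48. The shortfall against 38 completers is one person at best (89.5% power) and about four with 20% loss among those pending (86.6%).

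The loss of power is modest, and it is conditional on enrolment ending at Table 2's total. The power figures take the plan's effect size and correlation as given. The ceilings of 43 and 37 assume that all 13 pending people are randomised; the label does not say whether they have consented or been screened, and any further screen failure would lower both.

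The mismatches with the Table 1 footnote, 20 against 21 and three against five, are small. The first could reflect different count dates or a missed assessment. The main result does not depend on either.

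**What to change.** Take the screen failures out of Table 2's total line so that 48 means randomised, as the text says: 30 assigned to date plus 18 still to randomise. At 20% loss among the 18 this gives about 38 completers, in line with the Sample size section. The cost is a table edit and, against Table 2's projection, five more participants to randomise.

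If the sponsor prefers to keep 13 pending, restate the size in the text and the Sample size section as at most 43 randomised, with about 34 completers (at most 37) and about 87% power (at most 89.5%). This costs only a text change and a less favourable stated power.

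In either case, reconcile the post-intervention 2 count of 20 in the Table 1 footnote with the 21 completed in Table 2, and the three unassigned study numbers with the five screen failures. A count date on each table may be enough for the first.
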